### Randomization

2.9

Patients fulfilling the eligibility criteria will be enrolled in this study. Patients will be randomized to group 1; BOT reduction via TORS or group 2; CPAP or MAD. Blinding of patients or investigators will not be possible as interventions will make patients aware of the group they have been allocated to. Randomization is performed using sealed envelopes prepared in advance by an independent person who is not part of the research team and is not involved in participant recruitment, consent, procedures, eligibility assessment, treatment delivery or outcome assessment. The randomization list is not accessible to the research team. The list will be generated, and individual treatment assignments will be made available via sealed envelopes. Allocation will be performed by opening a sealed envelope, in strict sequential order, after the patient has provided written informed consent, to safeguard allocation concealment.

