### Study outcomes

2.5

The primary endpoint of this study is the mean AHI measured 6 months post-intervention. This time point was selected because it reflects the earliest clinically relevant assessment at which treatment effects are expected to be stable in both arms: after postoperative recovery following TORS and after establishment of CPAP/MAD use and adherence. The PG will be performed at baseline, 6 months and 12 months. A lower AHI reflects improved airway patency and is thus clinically meaningful in assessing treatment effectiveness between groups. Twelve month follow up is included as an important secondary endpoint to evaluate durability of treatment effects in this chronic condition. Secondary outcomes include: (1) 50% reduction of AHI at 6 months compared to baseline and or AHI below 20/h (Sher's criteria) [2,21] reduction of AHI at 12 months to <5/h will be defined as surgical cure [3,22] differences in mean ODI 4% values at 6 months and 12 months, and reduction of ODI 4% to 25% relative to baseline will be defined as clinically relevant [4,22] differences between FOSQ-35 [15] scores at 3 months, 6 months and 12 months in which an increase of 10% of the score compared to baseline on the FOSQ-35 questionnaire will be defined as clinically relevant [5,22] differences between scores of ESS at 3 months, 6 months and 12 months and a reduction on the ESS to <10 will be defined as clinically relevant [6,23] differences between scores of quality of life questionnaires EQ-5D-5L [19] at 3 months, 6 months and 12 months [7]; differences in scores on the visual analogue scales (VAS) for snoring, tiredness and globus in all patients between baseline, 3, 6 and 12 months [8]; VAS scores swallowing and taste for patients in the TORS group at baseline compared to 3 months, 6 months and 12 months.

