After inclusion and randomization, group 1 will undergo TORS and will be hospitalized post-surgery, which is expected to be 3 days. Patient will be discharged home with pain medication and will visit the outpatient clinic after 6 weeks for evaluation of surgical wounds. Group 2 will be assessed by either a pulmonologist or a MFO surgeon. They will have an evaluation of treatment after 3 months. Time point 0 (T0) starts when patient undergoes surgery and the first day of usage of CPAP or MAD. The TORS group will complete questionnaires at 3, 6 and 12 months and will undergo PG at 6 and 12 months for evaluation of the treatment. Then, they will also have evaluation of swallowing quality of the speech language pathologist at baseline, 2 days after surgery (while hospitalized) and 6 weeks. The CPAP or MAD group will have outpatient follow-ups at the pulmonologist or MFO surgeon at the same time points. Then, they will also complete the questionnaires (3,6 and 12 months) and will undergo PG at 6 and 12 months. The CPAP will be read out at 3,6, and 12 months. For the TORS group, in addition to standards PG and quality of life questionnaires, pain scores using VAS will be recorded. The length of hospital stay will also be monitored.

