### Sample size calculation

2.8

To answer our primary objective 25 patients per arm must be included in the study. This sample size calculation is based on results of an earlier RCT where OSA surgery was compared to conventional therapy (medical management) [26]. At 6 months MacKay et al. found the means of AHI to be in group 1, the conventional group 34.5 with a standard deviation of 23.0 and in group 2, the surgery group 20.8 with a standard deviation of 18.4. We have chosen to select a smaller standard deviation compared to the literature, as retrospective analysis of our database of OSA patients treated with TORS show a mean of AHI at 3 months (n = 31) of 16.4 with a standard deviation of 12.0 and a mean of AHI at 1 year (n = 14) of 10.8 with a standard deviation of 8.48. As our inclusion and exclusion criteria are strict and like our retrospective data and we expect a similar outcome. Given the sample size, analyses will primarily focus on estimating treatment effects with 95% confidence intervals. Secondary outcomes and subgroup analyses will be considered exploratory. Group sample sizes of 21 and 21 achieve 82% power to detect a difference of 10.0 between the null hypothesis that both group means are 34.0 and the alternative hypothesis that the mean of group 2 is 24.0 with estimated group standard deviations of 10.0 and 12.0 and with a significance level (alpha) of 0.05 using a two-sided two-sample *t*-test. The detectable differences are estimated to be of clinical relevance. To correct for possible missing data, we calculated a 20% bigger sample size which results in a sample size of 25 patients per arm.

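### The reason given for not blinding covers patients and treating staff only; it does not justify unmasked scoring of the sleep recordings that yield the primary AHI

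*Protocol article*

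**What the plan says.** Section 2.9 (Randomization) contains the only statement on blinding: "Blinding of patients or investigators will not be possible as interventions will make patients aware of the group they have been allocated to". The same section describes sealed envelopes prepared by an independent person who "is not involved in participant recruitment, consent, procedures, eligibility assessment, treatment delivery or outcome assessment", and opened "in strict sequential order, after the patient has provided written informed consent, to safeguard allocation concealment".

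Section 2.5 (Study outcomes) defines the endpoint: "The primary endpoint of this study is the mean AHI measured 6 months post-intervention". On how it is measured it says: "The PG will be performed at baseline, 6 months and 12 months". It also lists ODI 4% and the numbers of apneas and hypopneas among the sleep-recording measurements.

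Section 2.6 places control-arm follow-up with the treating specialties: "The CPAP or MAD group will have outpatient follow-ups at the pulmonologist or MFO surgeon at the same time points". The article does not say who scores the recordings, whether that person knows the arm, or whether control-arm recordings are made with the device in use.

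**The concern.** The sentence in section 2.9 draws a conclusion about two groups, patients and investigators, from a reason that concerns one. A patient who has had surgery or sleeps with a device knows it, and so do the clinicians who provide it. Scoring a recording is a separate task, and it does not by its nature require knowledge of the allocation.

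This matters because AHI rests on counted respiratory events, so the result depends on which events are scored. The trial is open-label and run at one hospital that provides the surgery, the CPAP and the MAD. If a scorer who knows the arm treats borderline events differently between arms, the shift passes in full into the difference in mean AHI. The planned primary analysis in section 2.10, an unadjusted t-test or Mann-Whitney test, cannot separate such a shift from a treatment effect. Section 2.8 puts the emphasis on estimates with 95% confidence intervals. A constant shift would move the whole interval without widening it, so the reported precision would give no warning.

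**Working it through.** **1. Who the stated reason covers**

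| Group | Does patients' awareness explain the lack of blinding? | What the article provides |
|---|---|---|
| Patients | Yes | Stated as unblinded (2.9) |
| Treating staff | Yes, by extension, since they deliver the treatment | Within 'investigators' (2.9) |
| PG scorer | No | Not mentioned |

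**2. Whether another safeguard fills the gap**

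- Section 2.9 does mention outcome assessment, but only to describe the independence of the person who prepares the envelopes. It does not say that assessors are masked.
- The sealed envelopes protect the allocation up to the moment of assignment. They do nothing for scoring at 6 or 12 months.
- The limitations in section 3 name the mixed control arm and the small sample. They do not mention assessors' knowledge of the arm.

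**3. The plan's own figure**

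Inputs from section 2.8: "Group sample sizes of 21 and 21 achieve 82% power to detect a difference of 10.0", with "estimated group standard deviations of 10.0 and 12.0", two-sided alpha 0.05, t-test.

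- SE = sqrt(10²/21 + 12²/21) = sqrt(244/21) = 3.41 events/h.
- Noncentrality = 10/3.41 = 2.93, df = 40.
- Power from the noncentral t distribution = 81.7% (81.6% with Welch degrees of freedom).

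The stated 82% reproduces, and this point does not alter it.

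**4. Illustration of what a scoring shift would do**

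The document gives no figure for scoring bias, so the shifts below are assumptions. Let *b* be a systematic between-arm shift in scored AHI when there is no true difference. The rejection rate is the noncentral t probability with noncentrality *b*/SE, where SE = 3.41 at 21 per arm and sqrt(244/25) = 3.12 at 25 per arm.

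| Assumed shift *b* (events/h) | Share of planned difference of 10 | Rejection rate, 21 per arm | Rejection rate, 25 per arm |
|---|---|---|---|
| 0 | 0% | 5.0% | 5.0% |
| 1 | 10% | 5.9% | 6.1% |
| 2 | 20% | 8.8% | 9.6% |
| 3 | 30% | 13.8% | 15.6% |
| 5 | 50% | 29.9% | 34.8% |

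A shift can also work against a real effect. With a true difference of 10 and a shift of 2 in the opposite direction, the test sees 10 − 2 = 8, and power at 21 per arm falls from 81.7% to 62.9%. With a shift of 2 in the same direction it sees 12, and power rises to 93.0%.

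These figures show how sensitive the test is to a shift of a given size. They are not evidence that any shift would occur.

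**The case against.** The strongest reply is that this is largely an argument from silence. A journal article condenses the full protocol, and the identity and masking of the PG scorer is a detail that the fuller document may hold. PG is also part of the centre's routine work-up (section 2.6), so the scorer need not be an investigator at all. This stands in part: the full protocol could name a masked scorer. The point does not rest on the omission alone, however. The article states a reason for not blinding investigators, and that reason does not support the conclusion. If masked scoring exists, the sentence should say so.

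A second reply is that masking may not be fully achievable. If control-arm recordings are made with CPAP in use, the trace may reveal the arm. This also stands. It limits how much masking can achieve but does not remove the case for it where traces are not revealing. A related reply is that the article does not say whether scoring is manual or automatic; fully automatic scoring without human correction would leave little room for this bias.

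A reader might also infer several stronger claims that the document does not support:

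- *That blinding is ruled out altogether.* The sentence names patients and investigators and is silent on scorers and analysts.
- *That AHI is the only objective endpoint left in an open-label trial.* ODI 4% is also objective. It comes from the same recordings, although the article does not say how far it depends on a scorer's judgement.
- *That such bias could never be detected afterwards.* If the recordings are kept, they can be re-scored under masking.
- *That the bias would favour surgery because surgeons at the centre deliver it.* The same hospital prescribes the CPAP and makes the MAD (section 2.3), and nothing says that any treating clinician scores the PG.

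**Conclusion.** The point holds in a limited form. The justification in section 2.9 covers patients and, by extension, treating staff. It does not justify unmasked scoring of the recordings that produce the primary AHI and ODI 4%, and the article provides no masked scoring. The primary comparison is therefore exposed to assessment bias of unknown size and unknown direction, which could be at least partly avoided.

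The conclusion assumes that a person makes or corrects scoring decisions, and that the full protocol holds no masking rule that the article leaves out. No size is claimed: the rejection rates depend entirely on assumed shifts. The change is worth making as an inexpensive safeguard for the primary endpoint. It does not show that the trial's result would be wrong.

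**What to change.** In section 2.9, limit the statement that blinding is impossible to patients and treating staff. Then add wording such as:

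> PG recordings at baseline, 6 and 12 months are exported under a study code without name, arm or visit. They are scored by staff who already score PGs, who are not involved in the patient's care and who are not told the allocation. Recordings for which masking cannot be achieved are identified as such, with the reason.

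The section should also state whether control-arm recordings are made with the device in use, since that determines how far masking can succeed. If the full protocol already provides for masked scoring, correcting the sentence in section 2.9 is enough.

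The cost is a coding step at export, and masking would be only partial for any recordings made on CPAP. Sample size, treatment and patient burden do not change. That existing staff can do this without an additional reader is an assumption for the sponsor to confirm. The rule should be in place before follow-up recordings are scored; any already scored could be re-scored under code if the recordings have been kept.

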### Statistical analysis

2.10

All statistical analyses will be conducted using IBM SPSS Statistics. The full analysis set (FAS) follows the Intention-To-Treat (ITT) principle and includes all planned subjects, except those with major protocol violations, no post-baseline data, or no study intervention.

Baseline characteristics, including age, gender, BMI, PG, ENT exam, DISE results, smoking, and reflux history, will be summarized using descriptive statistics. Quantitative variables will be presented as mean and standard deviation or as median with interquartile range or minimum/maximum, and qualitative data as frequencies and percentages, with 95% confidence intervals where applicable. Data normality will be assessed graphically and numerically. No formal statistical tests will be performed for baseline comparisons. The primary outcome (AHI at 6 months) will be analysed using independent *t*-test or Mann-Whitney *U* test depending on data distribution. Given the RCT design, adjustments for baseline differences are not foreseen. In case of missing data this will be mentioned in the results. Missing data will not be replaced. For all hypothesis testing, a two-sided p-value of less than 0.05 indicates statistical significance. Secondary outcomes will follow the same approach. For continuous variables, appropriate group comparisons (*t*-test, Mann–Whitney U, ANOVA, or Kruskal–Wallis) will be used. For categorical outcomes, Fisher's exact or Chi-square tests will be applied as applicable. Because the control arm includes two standard non-surgical modalities (CPAP and MAD), additional prespecified analyses will be performed to assess robustness. These include [1] subgroup analyses comparing TORS vs CPAP and TORS vs MAD separately (exploratory due to sample size) and [2] sensitivity analyses adjusting for control modality (CPAP vs MAD) when evaluating the primary endpoint. Treatment adherence data will be reported descriptively and considered when interpreting outcomes. Other study parameters will be analysed descriptively as outlined above.

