**Results:**

The data will be analysed on an Intention-To-Treat principle (ITT). Ethical approval was obtained from RTPO in September of 2023. Trial registration number: NL84446.099.23 METCnumber UMCG25.327. Outcomes will be published in peer reviewed journals and presented at (inter)national conferences.

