## Introduction

1

In obstructive sleep apnea (OSA) syndrome, repetitive partial or complete collapse of the upper airway during sleep leads to nocturnal hypoxia and interruption leading to daytime sleepiness [1]. OSA is associated with an increased risk of comorbidities such as hypertension, type 2 diabetes mellitus, and cardiovascular disease [2,3]. The gold standard treatment for OSA is continuous positive airway pressure (CPAP). CPAP effectively reduces apnea hypopnea index (AHI), improves sleep quality and decreases cardiovascular co-morbidities [4,5]. Regardless of the benefits, 30% of patients refuse treatment with CPAP due to several reasons including pressure effect of the mask [4] [[5], [6], [7]]. Another challenge of CPAP is treatment adherence, which requires a minimum usage of 4 h per night on at least 70% of nights. A study by Koehler et al. has shown that after 3 months adherence rates were 54% [8]. Mandibular advancement devices (MADs) are another non-surgical treatment modality that effectively reduce AHI [9], though they are less effective than CPAP. However, MADs demonstrate higher treatment adherence compared to CPAP [10].

For OSA patients who are unable to tolerate CPAP or MADs and are eligible for surgery, transoral robotic surgery (TORS) has emerged as an effective treatment option. TORS focuses on the obstruction at BOT, permanently enlarging the upper airway by removing lingual tonsil tissue. However, like all surgeries, TORS carries inherent risks such as postoperative bleeding, stenosis, infection and dysphagia, all risks that non-surgical therapies do not present. While studies have shown that TORS effectively reduces AHI [11,12], randomized trials comparing its efficacy to standard non-surgical therapies are lacking.

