### Study interventions

2.3

Participants randomized to the surgical arm will undergo TORS with BOT reduction, a technique established by Vicini et al. in 2010 [13]. In the Netherlands it is an accepted and well tolerated technique to reduce the BOT [14]. Procedures will be performed under general anaesthesia by two head and neck surgeons of the Frisius Medisch Centrum Leeuwarden, following standardized protocols. Postoperative care includes a short clinical stay of 3 days and a clinical follow-up visit at 6 weeks.

Participants randomized to the control arm will receive non-surgical therapy, consisting of the gold standard treatment, CPAP or MAD, as determined by shared decision-making between patient and their physician. CPAP devices (Airsense 10 AutoSet, Airsense 10 Elite, Airsense 11 Autoset or Airsense 11 Elite) will be prescribed by the pulmonologists of the Frisius Medisch Centrum Leeuwarden and will be tailored to patient needs. CPAP devices will be fabricated by ResMed. Adherence data will be remotely monitored.

Participants receiving MAD will be evaluated by a maxillofacial oral surgeon and fitted with custom adjustable devices manufactured by SomnoMed, SomnoDent Flex. The MAD will be made in the dental laboratory of the Frisius Medisch Centrum Leeuwarden.

CPAP and MAD users will receive standardized counseling regarding usage, side effects, and expectations. Technical or adherence issues will be addressed through telephone follow-up and in-person visits as needed.

The following interventions are prohibited during the trial period [1]: use of CPAP or MAD after intervention via TORS [2]; other concomitant transoral surgery such as (bi maxillary) osteotomy [3]; other concomitant OSA treatment such as position therapy, hypoglossal nerve stimulation, nasal resistors, oropharyngeal exercises.

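### The full analysis set is called ITT but drops randomised patients for major protocol violations or for receiving no intervention, so the primary AHI comparison is not ITT

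*Protocol article*

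**What the plan says.** The Abstract (Results) states: "The data will be analysed on an Intention-To-Treat principle (ITT". The Statistical analysis section (2.10) then defines one full analysis set, which "follows the Intention-To-Treat (ITT) principle and includes all planned subjects, except those with major protocol violations, no post-baseline data, or no study intervention". The same section adds: "Missing data will not be replaced". Its sensitivity analyses concern only the CPAP/MAD mix in the control arm.

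Three other sections bear on who could be excluded:

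- Study interventions (2.3): "The following interventions are prohibited during the trial period [1]: use of CPAP or MAD after intervention via TORS".
- Recruitment and screening (2.6): "Time point 0 (T0) starts when patient undergoes surgery and the first day of usage of CPAP or MAD". The 6- and 12-month PGs follow from that time point.
- Randomization (2.9): "Blinding of patients or investigators will not be possible". The envelope is opened after consent, so the arm is known before treatment starts.

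The article does not define a major violation. It also does not say whether PG in a TORS patient who has begun using a device is done with the device on or off.

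**The concern.** An ITT comparison keeps every randomised patient in the allocated arm, whatever treatment follows. Two of the three listed exclusions break that rule. Receiving no intervention necessarily follows randomisation. A major protocol violation may follow it too. Both can depend on the arm, because patients and investigators know the allocation.

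This trial has visible routes to such exclusions. A TORS patient with residual apnoea may start a prohibited device and be classed as a major violator. A patient in either arm may learn the allocation and never start. That patient also has no T0, so no 6-month PG date is defined. With 25 patients per arm, each removal carries weight in the primary endpoint, and the result would still be reported as ITT.

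**Working it through.** **Inputs.** From Sample size calculation (2.8): means 34 and 24, SDs 10 and 12, 21 per arm analysed, 25 randomised, two-sided alpha 0.05. The conventional arm of the earlier RCT cited there had a mean of 34.5. *Assumptions, because the documents give no figures:* excluded share p = 5, 10 or 20%; correlation r between AHI and starting a device of 0.3 to 0.5, with r = 1 as the extreme; AHI on a device as stated below.

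**Plan's own figure.** The SE is sqrt(100/21 + 144/21) = 3.41. A two-sample t-test for a difference of 10 has power 81.6 to 81.7%, against the stated 82%. It reproduces.

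**Step 1: TORS device users removed.** If a share p is removed on a score correlated r with AHI, the TORS mean falls by 12 × r × φ(z) / (1 − p), where z is the upper p point of the standard normal. Example: p = 10%, r = 0.5 gives 12 × 0.5 × 0.1755 / 0.90 = 1.17, so the difference is 11.17. If these patients are kept with an on-device AHI of a, the TORS mean is (1 − p)(24 − shift) + p × a.

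| Handling (true difference 10) | 5% | 10% | 20% |
|---|---|---|---|
| Kept, PG off device | 10.0 | 10.0 | 10.0 |
| Excluded, r = 0.3 | 10.39 | 10.70 | 11.26 |
| Excluded, r = 0.5 | 10.65 | 11.17 | 12.10 |
| Excluded, r = 1 (exactly the worst removed) | 11.30 | 12.34 | 14.20 |
| Kept, PG on device, a = 5, r = 0.3 | 11.32 | 12.53 | 14.81 |
| Kept, PG on device, a = 5, r = 0.5 | 11.57 | 12.95 | 15.48 |

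Exclusion therefore favours TORS relative to off-device PG. Relative to on-device PG it works against TORS whenever the on-device AHI is below the mean of the remaining TORS patients, which is 19.8 to 23.6 over these settings.

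**Step 2: false positives.** With no true difference, N(34, 10) against N(34, 12), 21 per arm, and 1, 2 or 4 TORS patients removed, 60,000 simulated trials give these rejection rates relative to off-device values:

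| r | 1 removed | 2 removed | 4 removed |
|---|---|---|---|
| 0.3 | 5.4% | 5.5% | 6.7% |
| 0.5 | 5.4% | 6.7% | 9.2% |
| 1 | 7.4% | 11.2% | 23.6% |

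A separate simulation with 25 per arm, removing the worst 1 or 2, gives about 7% and 11%.

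**Step 3: patients who never start.** If a share q has AHI 34.5 (assumed) and the treated patients average m, excluding the share lowers the arm mean by q × (34.5 − m).

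| Arm and m | 5% | 10% | 20% | Favours |
|---|---|---|---|---|
| TORS, m = 24 (planned) | 0.53 | 1.05 | 2.10 | TORS |
| Control, m = 20 (assumed) | 0.73 | 1.45 | 2.90 | Control |
| Control, m = 5 (assumed) | 1.48 | 2.95 | 5.90 | Control |
| Control, m = 34 (planned) | 0.03 | 0.05 | 0.10 | Control |

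**Step 4: combined.** Take 10% of TORS patients removed at r = 0.5 (1.17 towards TORS, relative to off-device PG) and 10% of controls removed as never-starters. The net shift is 1.17 − 0.05 = 1.12 towards TORS if device users average 34, and 2.95 − 1.17 = 1.78 towards control if they average 5. The sign is not determined.

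**The case against.** The strongest reply is that this is a labelling matter in a condensed article. What counts as a major violation, and whether a per-protocol set exists, is commonly left to the full protocol or SAP. That is fair for the definitions. It does not cover the stated rule: the article says such patients are removed from the set it calls ITT, and a later document could only cure this by overriding it.

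Several stronger readings are tempting but not supported:

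- *The exclusions would bias the result towards TORS.* Steps 1 and 3 show that the direction can reverse.
- *Device use after TORS is a major violation.* The article prohibits it but never calls it major. It could be so classed, and no more can be said.
- *All major violations arise after randomisation.* The term could also cover eligibility breaches, which precede it.
- *Control non-start will be common, because the Introduction says* "30% of patients refuse treatment with CPAP". That describes patients in general. Trial controls have consented to randomisation, are eligible for both arms, and may choose a MAD instead.

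The objection on size also stands in part. With one or two TORS patients removed at r = 0.3 to 0.5, the shift is 0.4 to 1.2 events/h, against a 95% confidence half-width of about 6.9 (2.02 × 3.41), and the error rate is 5.4 to 6.7%. The figure of 24% requires exactly the four worst of 21 to be removed.

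**Conclusion.** The rule is wrong as written. A set that drops randomised patients for receiving no intervention, or for violations that can follow randomisation, is not ITT and contradicts the Abstract. The contradiction rests on the text alone and needs no assumption about rates.

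The bias in the 6-month AHI difference is possible but undetermined in sign and size. Under the assumed shares it runs from a few tenths of an event/h to about 2 for TORS device users at moderate correlation, and to about 4 in the extreme case, measured against off-device PG. Excluding control never-starters moves the result the other way by between 0.03 and 5.9 events/h, depending on how well device users do. Since missing values are not replaced and no sensitivity analysis of the exclusions is described, a reader of the results could not see the effect. It should be changed before analysis.

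**What to change.** In Statistical analysis (2.10):

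1. Define the primary set as all randomised patients with a PG result at the time point, analysed in their allocated arm.
2. Delete major protocol violations and absence of study intervention as exclusions from that set. Use them only to define a per-protocol sensitivity analysis.
3. State that receiving the other arm's treatment is not a ground for exclusion.

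In Recruitment and screening (2.6), schedule the 6- and 12-month PG for patients who never start treatment, dated from randomisation because they have no T0. This gives them a different time origin from treated patients, which is preferable to having no outcome. Report non-start and crossover by arm.

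The cost is wording changes and a few extra scheduled PGs, with no additional patients. Under the plan's own assumptions, analysing all 25 per arm gives about 88% power. The price in interpretation is that the estimate reflects treatment as assigned, including non-start and crossover. That suits the pragmatic question the Introduction poses.

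### The full analysis set is labelled intention-to-treat but drops major protocol violators and never-treated patients, so the primary comparison is not of the randomised groups

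*Protocol article*

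**What the plan says.** The Abstract, under Results, states the principle: "The data will be analysed on an Intention-To-Treat principle (ITT". Section 2.10 (Statistical analysis) repeats it: "The full analysis set (FAS) follows the Intention-To-Treat (ITT) principle". The same sentence then defines the set as one that "includes all planned subjects, except those with major protocol violations, no post-baseline data, or no study intervention". It starts from planned rather than randomised subjects. The article names no other analysis set.

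Four further statements bear on how the exclusions would work:

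- Section 2.3 (Study interventions) lists among the prohibited interventions "use of CPAP or MAD after intervention via TORS".
- Section 2.5 (Study outcomes): "The primary endpoint of this study is the mean AHI measured 6 months post-intervention".
- Section 2.6 (Recruitment and screening): "Time point 0 (T0) starts when patient undergoes surgery and the first day of usage of CPAP or MAD".
- Section 2.10, on missing values: "Missing data will not be replaced".

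Section 2.9 says that neither patients nor investigators can be blinded. The robustness analyses listed in section 2.10 concern only the split of the control arm into CPAP and MAD.

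**The concern.** Intention-to-treat means that every randomised patient is analysed in the arm to which he or she was allocated, whatever happens next. A set that removes patients for violations or for not being treated is closer to a per-protocol set. The two descriptions in section 2.10 cannot both hold, and an analyst who follows the written exclusions will not produce the analysis that the Abstract announces.

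The routes to exclusion differ by arm and are taken with allocation known. On the surgical side a patient may decline the operation, or may go onto CPAP or MAD afterwards and so meet a listed prohibition. On the device side a patient may decline to start. These are different kinds of patient, so the groups left after exclusion need not be comparable. With 25 patients per arm, a handful of exclusions can matter.

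The time origin adds a practical problem. A patient who never has surgery and never uses a device has no time zero and hence no date for the 6-month polygraphy. Renaming the analysis set would not by itself produce a primary outcome for that patient.

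**Working it through.** **1. The label against the definition**

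| Exclusion in section 2.10 | Judged after randomisation? | Can differ by arm? | Conflicts with intention-to-treat? |
|---|---|---|---|
| Major protocol violation | Yes, or not excluded from being so | Yes; device use after TORS is prohibited in one arm only | Yes |
| No study intervention | Yes | Yes; declining surgery versus declining a device | Yes |
| No post-baseline data | Yes | Possibly | Little practical effect: with no AHI and no imputation, the patient cannot enter a t-test under any label |

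The point rests on the first two rows.

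**2. The plan's own figure**

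Inputs from section 2.8: 21 per arm, difference 10.0 (34.0 versus 24.0), SDs 10.0 and 12.0, two-sided alpha 0.05.

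- Standard error = √(10²/21 + 12²/21) = √(244/21) = 3.41
- Noncentrality = 10/3.41 = 2.93
- Power from the noncentral t = 81.6% (unequal variances) or 81.7% (pooled)

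The stated 82% reproduces. The sample-size arithmetic neither supports nor weakens the point. It supplies the 10/h yardstick.

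**3. Illustration, control arm**

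Let g be the share of controls who never start a device, and D the amount by which their AHI exceeds that of device users. Leaving them out lowers the control mean by g × D. Both are assumptions. For g, the upper value borrows the Introduction's statement that "30% of patients refuse treatment with CPAP due to several reasons".

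| g | D = 5 | D = 10 | D = 20 |
|---|---|---|---|
| 10% | 0.5 | 1.0 | 2.0 |
| 20% | 1.0 | 2.0 | 4.0 |
| 30% | 1.5 | 3.0 | 6.0 |

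A lower control mean makes TORS look worse.

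**4. Illustration, TORS arm**

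Let f be the share of the TORS arm never operated on, assumed to stay at 34 while operated patients average 24. The restricted set estimates 10.0. All randomised patients estimate 10 × (1 − f). One patient of 25 therefore moves the estimate by 10 × 1/25 = 0.4/h.

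For power with 25 + 25 randomised, the TORS variance is taken as 12²(1 − f) + 10²f + 10²f(1 − f).

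| Never operated on, of 25 | Restricted-set difference | All-randomised difference | Power, 25 + 25 |
|---|---|---|---|
| 0 | 10.0 | 10.0 | 88% |
| 1 | 10.0 | 9.6 | 85% |
| 2 | 10.0 | 9.2 | 82% |
| 3 | 10.0 | 8.8 | 78% |
| 4 | 10.0 | 8.4 | 74% |
| 5 | 10.0 | 8.0 | 70% |

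Here exclusion makes TORS look better. Steps 3 and 4 push the contrast in opposite directions, so the net bias cannot be predicted.

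**The case against.** The contradiction itself is hard to dispute. The strongest case on the other side concerns how far it can be pushed, and most of that case stands.

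- **Surgical failures.** A reader might infer that dropping device users from the TORS arm flatters surgery by several events per hour. Model TORS AHI as a gamma distribution with mean 16.4 and SD 12.0. Trimming the worst 10% or 20% then gives 13.5 or 11.6, shifts of 2.9 and 4.8/h. The documents do not support that reading. Section 2.8 gives 16.4 as a 3-month database mean, not a 6-month one, and trimming exactly the worst patients is the extreme case. Patients kept in the set after going onto a device would plausibly be measured on it. At an assumed on-device AHI of 10, the retained mean is 0.9 × 13.47 + 0.1 × 10 = 13.1, or 0.8 × 11.63 + 0.2 × 10 = 11.3. The shift then nearly vanishes, at about 0.3/h with the opposite sign.
- **The 30% rate.** It refers to refusal of CPAP. Controls here may choose CPAP or MAD, are eligible for both arms and consent before allocation, and patients unable to tolerate MAD are excluded. A 30% non-start rate is a pessimistic end of a range, not a forecast.
- **Who judges a violation, and why the trial exists.** The article does not say that the study team decides which violations are major. Nor does it make non-uptake the reason for the comparison; the Introduction rests it on the place of surgery in the care pathway. Neither inference is used here.
- **Detail left to a fuller document.** A definition of a major violation, or a further analysis set, may stand in the full protocol or analysis plan. Their absence from the article is not the point. The conflict is between statements that the article does make.

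**Conclusion.** The point holds in this form: the article states an intention-to-treat analysis and, in the same sentence as its definition, excludes major protocol violators and never-treated patients. Followed as written, the primary test does not compare the randomised groups. A never-treated patient also has no defined 6-month assessment.

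The bias arises only if such patients occur, and its size and net direction are unknown. The illustrations rest on assumed non-start rates, an assumed AHI gap of 5 to 20/h, and untreated TORS patients staying at 34. They show only that plausible shifts in one arm run from a fraction of a unit to several units against a planned 10/h. They do not show that the result will favour either arm. The matter should be settled before outcomes are seen, because it fixes the primary comparison.

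**What to change.** 1. Define the primary analysis set as all randomised patients, analysed in the allocated arm regardless of treatment received or protocol violation.
2. Seek the 6-month polygraphy from every patient. For those who never start treatment, count the date from randomisation. Record whether a device was in use at the polygraphy.
3. Keep the present restricted set, renamed per-protocol, as a sensitivity analysis.
4. Report by arm the patients with no 6-month AHI. They stay out of the unimputed t-test whichever set is used.

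The cost is a paragraph of wording and a few extra polygraphy attempts; the examination is already scheduled in both arms. There are two downsides. The estimate is diluted by non-uptake, with the loss of power shown in the TORS table above. Never-starters are also timed on a different clock from everyone else, which should be stated when the results are reported.
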